# Does endometrial scratching increase the rate of spontaneous conception in couples with unexplained infertility and a good prognosis (Hunault > 30%)? Study protocol of the SCRaTCH-OFO trial: a randomized controlled trial

**DOI:** 10.1186/s12884-018-2160-z

**Published:** 2018-12-29

**Keywords:** Endometrial injury, Endometrial scratching, Endometrial scratch, Unexplained infertility, Endometrial receptivity, Implantation failure, Hunault > 30%, Expectant management

## Abstract

**Background:**

In the Netherlands, couples with unexplained infertility and a good prognosis to conceive spontaneously (i.e. Hunault > 30%) are advised to perform timed intercourse for at least another 6 months. If couples fail to conceive within this period, they will usually start assisted reproductive technology (ART). However, treatment of unexplained infertility by ART is empirical and can involve significant burdens. Intentional endometrial injury, also called ‘endometrial scratching’, has been proposed to positively affect the chance of embryo implantation in patients undergoing in vitro fertilization (IVF). It might also be beneficial for couples with unexplained infertility as defective endometrial receptivity may play a role in these women. The primary aim of this study is to determine whether endometrial scratching increases live birth rates in women with unexplained infertility.

**Method:**

A multicentre randomized controlled trial will be conducted in Dutch academic and non-academic hospitals starting from November 2017. A total of 792 women with unexplained infertility and a good prognosis for spontaneous conception < 12 months (Hunault > 30%) will be included, of whom half will undergo endometrial scratching in the luteal phase of the natural cycle. The women in the control group will not undergo endometrial scratching. According to Dutch guidelines, both groups will subsequently perform timed intercourse for at least 6 months. The primary endpoint is cumulative live birth rate. Secondary endpoints are clinical and ongoing pregnancy rate; miscarriage rate; biochemical pregnancy loss; multiple pregnancy rate; time to pregnancy; progression to intrauterine insemination (IUI) or IVF; pregnancy complications; complications of endometrial scratching; costs and endometrial tissue parameters associated with reproductive success or failure. The follow-up duration is 12 months.

**Discussion:**

Several small studies show a possible beneficial effect of endometrial scratching in women with unexplained infertility trying to conceive naturally or through IUI. However, the quality of this evidence is very low, making it unclear whether these women will truly benefit from this procedure. The SCRaTCH-OFO trial aims to investigate the effect of endometrial scratching on live birth rate in women with unexplained infertility and a good prognosis for spontaneous conception < 12 months.

**Trial registration:**

NTR6687, registered August 31st, 2017.

**Protocol version:**

Version 2.6, November 14th, 2018.

## Background

Unexplained infertility is diagnosed in up to 50% of infertile couples when standard fertility investigations have failed to detect any gross abnormality [1–3]. Uncertainty about the underlying reasons of the infertility often leads to use of empirical treatment that can involve significant physical, psychological and financial burdens [4]. Hence prediction models have been developed to distinguish subfertile couples with a poor prognosis for spontaneous pregnancy, for whom fertility treatment is thought to increase their chance of conception, from subfertile couples who still have a good prognosis to conceive spontaneously [5]. In the Netherlands, the prediction model developed by Hunault et al. (2004) is used to predict the chance of spontaneous pregnancy within 1 year. As stated in Dutch guidelines [3], couples with unexplained infertility and a prognosis according to Hunault of > 30%, i.e. a good prognosis, are advised to perform timed intercourse for at least another 6 months. If couples fail to conceive within 6 months to a year, they will usually start assisted reproductive technology (ART), i.e. intrauterine insemination (IUI) or in vitro fertilization (IVF) [3]. IUI or IVF treatment for this diagnosis, however, is empirical and is mainly done due to the perceived need to intervene to address unexplained infertility.

In previous research it has been postulated that defective endometrial receptivity, with altered expression of adhesive molecules and immunological factors, could be a contributing factor in the aetiology of unexplained infertility [4, 6–9]. At present, moderate-quality evidence indicates that endometrial injury (‘scratching’) is associated with an improvement in live birth rates (LBR) in women undergoing IVF with repeated failed embryo transfers [10]. Several hypotheses supporting the positive effect of scratching on pregnancy rates have been proposed, but the exact mechanism remains unclear [11]. The endometrial injury is thought to incite changes, like induction of decidualization and immunologic responses, which result in improved endometrial receptivity [10]. Since defective endometrial receptivity may be a cause of subfertility in couples diagnosed with unexplained infertility, scratching may be an effective therapy for these couples. Although the majority of studies showed a positive effect of scratching on pregnancy outcomes in women undergoing IVF, some recent studies did not find endometrial scratching to be effective in improving pregnancy outcomes in IVF [12, 13]. As significant clinical heterogeneity in study populations exist between studies, the applicability of the evidence may vary in different subgroups of subfertile women [10].

The effectiveness of scratching in couples trying to conceive through sexual intercourse or IUI was recently summarized in a review [14]. The main conclusion was that scratching may have a beneficial effect on the chance of conceiving, but that published studies have important limitations. Therefore these results should be interpreted with caution. Since publication of this review, one other study on endometrial injury in women with unexplained infertility has been published, reporting a non-significant difference in clinical pregnancy rates (CPR) between the intervention and control group (16.7 vs. 11.7%) [15]. Notably, this study was not adequately powered to detect the observed difference; a difference which may be clinically relevant. Furthermore, none of the published studies reported live birth rate as an outcome parameter, which is the most important outcome for a couple trying to conceive. Finally, there remains a paucity of evidence on the duration of the effect of endometrial scratching, making it unclear for how long the beneficial effect of the scratch is sustained. These observations underline the need for more robust studies on this topic.

The primary aim of the SCRaTCH-OFO study is to determine whether endometrial scratching in the natural cycle in women with unexplained infertility increases the chance of live birth. Parallel to this, it aims to evaluate if endometrial scratching leads to a decreased use of fertility treatment and costs needed to achieve a live birth. Finally, the RCT contains a nested cohort study in which endometrial samples will be banked to determine characteristics associated with reproductive success or failure within 12 months of follow-up.

## Method

### Study objective & design

The aim of this study is to evaluate whether endometrial scratching increases the chance of live birth in women with unexplained infertility and a good prognosis to conceive spontaneously (Hunault > 30%). Furthermore, the study seeks to determine endometrial characteristics correlating with (un) successful implantation and to develop endometrial organoids.

The SCRaTCH-OFO study is a multicentre randomized controlled trial (RCT) coordinated by the University Medical Centre Utrecht (UMC Utrecht, The Netherlands), which will be performed within the Dutch Consortium for Healthcare Evaluation and Research in Obstetrics and Gynecology. A prospective cohort study is embedded within the multicentre RCT, in which the endometrial biopsy will be banked for determination of characteristics associated with reproductive success or failure and for development of endometrial organoids that will open possibilities for further research into endometrium related disorders. Some of the study methods of this trial will be comparable to those previously described in the study protocol of our other scratching trial, in which scratching is performed in women undergoing IVF/intracytoplasmic sperm injection (ICSI) cycles [16].

#### Study population

Women from couples diagnosed with unexplained infertility and a Hunault of > 30%, who have been advised to continue timed intercourse during at least 6 months, are eligible. Inclusion criteria are as follows: female age between 18 and 38 years; primary or secondary infertility lasting at least 12 months; a regular menstrual cycle (defined as a mean cycle length of 21–35 days); at least one patent tube (diagnosed by negative Chlamydia antibody titre (CAT) and absence of risk factors for tubal disease, and/or diagnosed by hysterosalpingography or diagnostic laparoscopy); total motile sperm count > 3 million and a normal transvaginal ultrasound, which is defined as the absence of visible intracavitary pathology (e.g. polyps or intramural myomas with distortion of the uterine cavity). Exclusion criteria are: a history of lower abdominal or pelvic infection, a higher chance of intra-abdominal infection due to intestinal surgery, endometriosis grade 3 and 4, previous caesarean section with niche development, recurrent miscarriage (defined as ≥2 pregnancy losses prior to 20 weeks of gestation), the presence of untreated unilateral or bilateral hydrosalpinx, previous endometrial scratching, meno-metrorrhagia, and untreated endocrine disorders.

### Study endpoints

The primary endpoint is cumulative live birth rate, of which the status of ‘ongoing pregnancy’ should be achieved within 12 months after randomization, and is defined as the delivery of at least one live fetus ≥24 weeks of gestation. Secondary endpoints include 1) ongoing pregnancy rate, defined as the detection of a fetal heartbeat on ultrasound at a gestational age of 10–12 weeks; 2) clinical pregnancy rate, defined as a gestational sac visualized on ultrasound; 3) miscarriage rate, defined as a demise of an intrauterine pregnancy confirmed by ultrasound or histology; 4) biochemical pregnancy loss, defined as a spontaneous pregnancy demise after serum or urinary bèta-hCG had been detected, without an ultrasound evaluation; 5) multiple pregnancy rate; 6) time to pregnancy, defined as the time from randomization till a positive pregnancy test; however, only pregnancies that will reach the ‘ongoing’ status will be included in the analysis; 7) progression to IUI or IVF treatment; 8) pregnancy complications; 9) complications of endometrial scratching (e.g. abnormal bleeding, abnormal vaginal discharge, abdominal pain, fever); 10) costs; 11) endometrial tissue parameters associated with reproductive success or failure, such as endometrial gene expression profiles (EGPs).

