### Sample size calculation

A total of 792 women will be included in the RCT of which we expect 150 to be included in the embedded study. Based on previous studies, the estimated difference in live birth rate is at least 10% between the patients with and without endometrial scratch (live birth rate respectively 45% vs. 35%).To detect such a difference with 80% power, 396 patients are needed per study arm, resulting in 792 patients in total. This number takes into account an estimated dropout rate of 5%.

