### Data collection and data analysis

Data will be collected in a web based registration system. Database cleaning will consist of internal consistency checks and identification of database entries outside expected ranges. Analysis will primarily be conducted according to the intention-to-treat principle. In case many women allocated to the intervention group ended up not having the scratch procedure (or vice versa), a per-protocol analysis may also be performed to clarify whether there may have been an underestimation of the magnitude of effect. The researchers performing the data collection and data analysis are not blinded to group allocation.

SPSS Statistics (IBM Corporation, Armonk, NY, United States), R (R Foundation, New Zealand) and Excel (Microsoft, Washington, United States) will be used to perform the statistical analysis. The primary and secondary outcome variables (except the costs, of which analysis is described below) will be compared between the treatment arms and expressed as relative risk with 95% confidence interval. A *p*-value less than 0.05 will be considered to indicate a statistically significant difference.

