### Cost-effectiveness analysis

A cost-effectiveness analysis covering a period of 12 months will be performed parallel to the clinical trial for economic evaluation, which is designed from both a healthcare and societal perspective. This cost-effectiveness analysis will be based on live birth rate and average costs per patient, taking into account any additional fertility treatments patients undergo during these 12 months. The impact on patient’s life will be expressed in quality-adjusted life years (QALY). A decision model will be used to evaluate the optimal strategy, taking into account the time to pregnancy, (in) direct costs and estimated QALY. Additionally, the incremental cost-effectiveness ratio (ICER) and long-term costs, such as delivery and perinatal costs, will be determined. Sensitivity analysis will define robustness of the results.

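### Time to pregnancy is restricted to pregnancies that become ongoing and falls under a blanket relative-risk rule; neither gives a valid comparison of time to event between the arms

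*Protocol article*

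**What the plan says.** The protocol article, Study endpoints, lists as its sixth secondary endpoint "time to pregnancy, defined as the time from randomization till a positive pregnancy test", and adds that "only pregnancies that will reach the ‘ongoing’ status will be included in the analysis". It does not say what happens to women who have no such pregnancy.

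Data collection and data analysis sets one effect measure for all endpoints, primary and secondary alike: they "will be compared between the treatment arms and expressed as relative risk with 95% confidence interval". Costs are the only exception, so time to pregnancy is covered. Intention to treat is named as the primary principle, and no time-to-event method is mentioned.

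Three other places bear on the point:
- Study procedure tells women in the scratch arm to make sure they are not pregnant in the scratch cycle. The Fig. 2 legend places the scratch in the same or the next month after randomisation.
- Study procedure and Follow-up start the clock at randomisation in both arms, and follow-up lasts 12 months.
- Cost-effectiveness analysis says: "A decision model will be used to evaluate the optimal strategy, taking into account the time to pregnancy", together with costs and estimated QALYs.

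**The concern.** Whether a woman reaches an ongoing pregnancy is an outcome that scratching is meant to change. If only those pregnancies enter the analysis, the two groups compared are selected by outcome, and randomisation no longer makes them comparable. Mean time among women who conceive also says little about how quickly conception occurs in the whole arm, because women who have not conceived by 12 months carry much of that information and are left out.

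The effect measure does not repair this.
- Among ongoing pregnancies only, every record is an event, so there is no risk to compare.
- Among all randomised women, a relative risk for this event ignores the times. With the planned rates it would be 0.45/0.35 = 1.29 whether conceptions came early or late, which repeats the ongoing-pregnancy-rate endpoint.

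At stake is a named secondary endpoint that could show almost nothing, or the wrong direction, when scratching works. The article says that those who collect and analyse the data are not blinded, so the choice between readings should not be left until the data are seen.

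**Working it through.** **Inputs from the article.** "live birth rate respectively 45% vs. 35"% (Sample size calculation); 80% power and 5% dropout (same section); significance level 0.05; 12 months of follow-up; the scratch-cycle instruction and timing (Study procedure, Fig. 2 legend); mean cycle length 21–35 days (Study population).

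**Assumptions not in the article.** Constant hazards; live-birth rates standing in for ongoing-pregnancy rates; the scratch-cycle instruction modelled as a delay of d months from randomisation in the scratch arm only.

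**1. The plan's own figure.** Two-sided 0.05, pooled variance under the null:

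n = [1.960·√(2·0.40·0.60) + 0.842·√(0.45·0.55 + 0.35·0.65)]² / 0.10² = (1.358 + 0.580)² / 0.01 ≈ 375.6, so 376 per arm.

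376/0.95 = 395.8, so 396 per arm and 792 in total. This reproduces the stated sample size.

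**2. Who would enter a literal analysis.** 396·0.35 ≈ 139 control and 396·0.45 ≈ 178 scratch women, 317 of 792 (40%). The other 60% leave because of their outcome.

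**3. Hazards.** Control: −ln(0.65)/12 = 0.03590 per month. Scratch: −ln(0.55)/12 = 0.04982 per month. Hazard ratio 1.39.

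**4. Mean time among conceivers, no delay.** With p the 12-month rate, mean = 1/h − 12·(1 − p)/p.
- Control: 27.856 − 22.286 = 5.57 months.
- Scratch: 20.072 − 14.667 = 5.41 months.

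The difference is −0.16 month. A 39% higher hazard almost disappears, but the sign is right.

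**5. Adding a delay, two ways.**

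(a) Hold the scratch rate at 45% by 12 months. The mean becomes d + (12 − d)·(5.406/12), so the difference from control is −0.165 + 0.5495·d.

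| d (months) | Scratch mean | Difference from control |
|---|---|---|
| 0 | 5.41 | −0.16 |
| 0.5 | 5.68 | +0.11 |
| 1 | 5.96 | +0.38 |

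The sign changes at d = 0.165/0.5495 = 0.30 month. One cycle of 21–35 days is 0.69–1.15 months (at 30.4 days per month), which gives +0.21 to +0.47.

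(b) Hold the scratch hazard at 0.04982 and lose 1 month. With L = 11, exp(−hL) = 0.578, so 42% conceive by 12 months. Mean = 1 + 20.072 − 11·0.578/0.422 = 6.00 months, a difference of +0.43, although 42% vs 35% conceive.

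**6. Sensitivity to the window.** With an assumed 9.5-month conception window the pattern is the same: 4.41 vs 4.28 months without delay, +0.42 with 1 month lost under (a), and the sign changing at about 0.24 month.

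**7. Simulation.** 2,000 trials, 376 per arm, true rates 45% vs 35%. A t-test among conceivers, chosen here for illustration, is set against a log-rank test in all randomised women.

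| d (months) | Conceivers: significantly faster | Conceivers: significantly slower | Log-rank favours scratch |
|---|---|---|---|
| 0 | 7% | 0.9% | 82% |
| 1 | 0.2% | 18% | 74% |

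At d = 1 the scratch-arm mean among conceivers was the longer one in 86% of trials.

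**The case against.** The strongest reply is that the clause speaks of pregnancies, not women. It may only define the event, so that a positive test followed by biochemical loss or miscarriage does not count. The primary endpoint is tied to ongoing status in the same section, and intention to treat is the stated principle. On that reading all randomised women stay in, and the restriction is valid. This stands as a possible reading. The text does not say it, however, and it leaves the relative-risk sentence unsuited to this endpoint.

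It can also be said that the relative-risk sentence is shorthand in a condensed article and that survival methods belong in the full protocol or analysis plan. Silence on Kaplan–Meier curves or censoring would indeed be no finding. But the sentence names costs as its one exception and so assigns a specific, unsuitable measure to this endpoint. The article names no mean or t-test either; the figures above illustrate what a conceivers-only comparison would show.

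Three stronger conclusions might be inferred, and the article does not support them:
- That restricting to ongoing pregnancies by itself makes scratching look slower. Without a delay the restricted mean still favours scratching slightly.
- That 2 months are lost, which would give a gap of about 1 month. The instruction covers the scratch cycle only; avoiding conception while waiting for that cycle is not stated.
- That a biased time enters the decision model. Cost-effectiveness analysis says only that time to pregnancy is taken into account, not that this contrast is used.

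**Conclusion.** The point holds with limits. As written, the plan either compares times within a subset defined by the outcome or applies a measure that cannot express time to event; both readings need correcting. Under the stated assumptions, a hazard ratio of 1.39 shrinks to a 0.16-month difference among conceivers. About 1 month lost to the scratch cycle turns this into an apparent slowing of about 0.4 month, although more scratch-arm women conceive. The instruction behind the delay is in the article; its length, the constant hazards and the use of live-birth rates are assumptions.

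The reach is one secondary endpoint, and the decision model only if it takes its arm comparison of time to pregnancy from this analysis. The primary analysis and sample size are unaffected. It should be fixed before analysis, but it does not threaten the trial's main conclusion.

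**What to change.** In Study endpoints, replace the clause with wording such as: *Time to pregnancy runs from randomisation to the positive test of a pregnancy that becomes ongoing within the same 12-month window as the primary endpoint. All randomised women are analysed; women without such a pregnancy are censored at the end of that window or at last contact, if earlier. Cumulative incidence curves and a hazard ratio with 95% CI will be reported.* Add a note that the scratch cycle may make hazards non-proportional early on, so the curves should be read alongside the hazard ratio.

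In Data collection and data analysis, exempt time to pregnancy from the relative-risk sentence, as is done for costs. In Cost-effectiveness analysis, state that any arm comparison of time to pregnancy in the decision model uses the all-randomised estimate.

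The cost is a few sentences. The date of the positive test is already implied by the endpoint's definition. The article does not list a last-contact date, so check that it is recorded. The aim of counting only conceptions that become ongoing is kept.

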### Sample size calculation

A total of 792 women will be included in the RCT of which we expect 150 to be included in the embedded study. Based on previous studies, the estimated difference in live birth rate is at least 10% between the patients with and without endometrial scratch (live birth rate respectively 45% vs. 35%).To detect such a difference with 80% power, 396 patients are needed per study arm, resulting in 792 patients in total. This number takes into account an estimated dropout rate of 5%.

### Study procedure

In the intervention group, an endometrial scratch will be performed once before starting 6 months of timed intercourse, during the luteal phase of the natural cycle. Women are instructed to use urinary ovulation prediction tests that detect the putative luteinizing hormone (LH) surge (Ovulady, Clindia Benelux B.V., The Netherlands). The scratch will be performed 6 or 7 days after a positive urine ovulation test by a dedicated gynaecologist or fertility physician. If scheduling on this day is impossible then the scratch can also be planned 5 or 8 days after a positive ovulation test. Women will receive instructions that they need to make sure that they are not pregnant in the scratch cycle (no sexual intercourse or sexual intercourse with appropriate contraceptive methods (e.g.condoms)). After cleansing of the cervix with betadine, an endometrial biopsy catheter will be introduced into the cervix up to the uterine fundus. In most cases this will be a Pipelle de Cornier® biopsy catheter, but the type of biopsy catheter may vary per participating centre. The piston will be drawn back to the end of the biopsy catheter. Then the catheter is slowly retracted while rotating over several ranges of 360 degrees during 1 to 2 min. The protocol differs slightly for the subgroup of whom endometrial tissue will be stored. Firstly, a sterile gown, gloves and cap will be worn during the procedure in order to minimalize RNase contamination. Secondly, cleaning of the cervix will not be performed with betadine but with sterile saline solution (sodium chloride 0.9%) because the outcomes of RNA analysis could be affected by betadine. In order to minimalize RNase contamination, sterile gloves are changed for new gloves directly after the procedure. The endometrial tissue will be divided into three equal parts and each part will be stored in a Tissue Sampling Storage Tube (3 ml, Cat. No. 68–4000-00, Fluid X). In the coordinating centre (UMC Utrecht) and in one of the participating centres (Diakonessenhuis), two tubes will be snap-frozen in liquid nitrogen and one tube will be used to collect tissue for slow freezing of cells for organoid development. In the other tissue-storing centres, three tubes will be snap-frozen. The process of snap-freezing is performed within maximally 3 min from taking the biopsy. Subsequently, the snap-frozen tissue will be stored in freezers at − 80 °C until later determination of RNA profiles. Due to rapid developments in the field of genetics, the suited gene sets and techniques will be determined at the time of tissue analysis. The endometrial tissue intended for development of endometrial organoids will first be slow-frozen in medium containing dimethylsulfoxide (DMSO) and then stored in liquid nitrogen at − 196 °C until later formation of endometrial organoids. For this latter procedure the technique published by Boretto et al. (2017) [17] will be used.

Both the intervention and control group will undergo at least 6 months of timed intercourse from the moment of randomization. An overview of the study design and a study time schedule can be found in respectively Fig. 1 and Fig. 2.

